### Aims and hypotheses

The study hypotheses and research questions are presented in Table 1. The primary aim is to examine the effectiveness of CIPE, delivered approximately 1 to 2 months after a trauma, as an indicated secondary prevention aimed at reducing PTSS and the incidence of PTSD. We will compare the effect of CIPE + treatment as usual (TAU) vs. TAU only, to examine whether CIPE has the potential to improve the ordinary psychosocial services provided by crisis teams. In such contexts, TAU (see “TAU” under the section “Interventions”) is considered to be an appropriate comparator with several benefits [26, 27]. TAU reflects the current real-world practice of the psychosocial crisis teams against which any added benefit of CIPE must be demonstrated, in order to evaluate if CIPE improves standard care and should be routinely implemented in Norwegian municipalities. The study was designed as an add-on trial (i.e., CIPE as an add-on) due to practical and ethical considerations.

**Table 1 Tab1:** Hypotheses and research questions in the EASE study

Hypotheses concerning the effectiveness and cost-effectiveness of CIPE	
H1	Participants receiving CIPE + TAU will have significantly less PTSS than participants receiving TAU at 6 weeks post T1, and at 6 and 12 months after the traumatic incident
H2	Significantly fewer participants receiving CIPE + TAU will fulfill the criteria for PTSD compared to participants receiving TAU, at 6 and 12 months post trauma
H3	Participants receiving CIPE + TAU will have significantly less symptoms of depression and insomnia than participants receiving TAU at 6 weeks post T1, and at 6 and 12 months after the traumatic incident
H4	Participants in the CIPE + TAU-condition will report significantly higher treatment satisfaction at post-treatment, compared to those in the TAU-condition
H5	Participants with traumatic loss receiving CIPE + TAU will have significantly less symptoms of prolonged grief than participants with traumatic loss receiving TAU 12 months after the loss
H6	Fewer participants in the CIPE + TAU-condition will be referred to second-tier specialty mental health services, and more will achieve improved quality of life within the first year after the traumatic incident, compared to participants in the TAU-condition
H7	The CIPE + TAU implementation is more cost-effective compared to TAU in the short run and may even dominate TAU in the long run (i.e., more effective and less costly)

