### Statistical analyses

H1–3 are tested with linear mixed effects models. The linear mixed effects model includes fixed effects for treatment group (intervention vs. control) and time (post-intervention, 6 and 12 months). In a hierarchical setup, a second step includes a treatment × time interaction. Random effects include random intercepts for participants to account for individual differences. The mixed effects models are applied using the R package nlme [70]. H4–6 are examined using independent t-tests. The quality-of-life change (change in QALY) of participants in CIPE vs. TAU (H6) is analyzed using the mixed effects model. Estimation is conducted using restricted maximum likelihood, with all available observations included, yielding unbiased estimates under the assumptions of missing at random or missing completely at random. For the t-tests, missing data are handled using multiple imputation.

Hypothesis 7 involves a comprehensive economic evaluation comparing the cost-effectiveness of CIPE relative to TAU in terms of both costs and consequences/effectiveness [71]. Costs are assessed using the ingredients approach, which involves three steps: first, identifying each resource required for the intervention; then, measuring these resources; and finally, valuing them. The effectiveness of the intervention is measured by QALY—a composite measure combining both quantity of life (mortality) and quality of life (morbidity) into a single metric [72]. For each arm, mean costs and mean QALYs are estimated across all participants to calculate the incremental cost (ΔC) and incremental effect (ΔQALY). The incremental cost-effectiveness ratio (ICER) or incremental cost per incremental QALY (ΔC/ΔQALY) is then calculated for decision-making. To accept the intervention, ICER should be less than the willingness-to-pay or cost-effectiveness threshold. Since there is no official threshold in Norway, we apply a threshold recommended by the Norwegian Directorate of Health (NOK 500 000 at 2005 prices), adjusted to current price levels [73].

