This economic evaluation is conducted in two ways: trial- and model-based approaches. In the former, we compare trial-specific intervention costs and effects. Following recommendations by NICE [74], we perform a cost-utility analysis combining intervention-related and wider healthcare costs with changes in QALYs. In the latter, we develop a decision analytic model to simulate the long-term (lifetime) cost-effectiveness of CIPE. The model extrapolates beyond the trial period to estimate the potential lifetime costs and QALY outcomes under different assumptions. In both approaches, model parameter uncertainty is assessed using both probabilistic and deterministic sensitivity analyses.

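### The only stated cost-effectiveness rule, ICER below the threshold, is valid only when the QALY difference is positive, and the plan does not say so

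*Protocol article*

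**What the plan says.** Under Statistical analyses, the article describes the economic evaluation for H7. Costs and QALYs are summarised by arm: "For each arm, mean costs and mean QALYs are estimated across all participants to calculate the incremental cost" and the incremental effect. The ratio is given a decision role: "incremental cost per incremental QALY (ΔC/ΔQALY) is then calculated for decision-making". One acceptance rule follows: "To accept the intervention, ICER should be less than the willingness-to-pay or cost-effectiveness threshold". The threshold is the Norwegian Directorate of Health figure of NOK 500,000 at 2005 prices, to be inflated; the inflated value is not stated.

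For both the trial-based and the model-based evaluation, the same section adds that "model parameter uncertainty is assessed using both probabilistic and deterministic sensitivity analyses". It states no other decision rule. Dominance appears only in Table 1, where H7 says that CIPE + TAU "may even dominate TAU in the long run (i.e., more effective and less costly").

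**The concern.** A cost-effectiveness ratio loses the signs of its two parts. A negative ratio arises when CIPE is better and cheaper, and also when it is worse and dearer. A positive ratio arises when CIPE is better and dearer, and also when it is worse and cheaper. A rule that compares the ratio alone with a threshold is therefore sound on only one side of the cost-effectiveness plane, where ΔQALY is positive.

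The restriction is not a formality here. CIPE is added on top of TAU, so delivery costs are added too, and a positive ΔC with a ΔQALY near zero is a realistic result. H7 itself looks outside the costlier, more effective quadrant by raising dominance. At stake is the H7 decision, which is secondary but is meant to inform routine use in the municipalities. The share of probabilistic draws counted as cost-effective is also at stake, if the written rule is applied draw by draw.

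**Working it through.** **Inputs from the article.** ICER = ΔC/ΔQALY. Accept if ICER < λ, with λ = NOK 500,000 at 2005 prices, inflated. The article reports no result of this rule, so there is no figure to reproduce.

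**Assumed inputs.** λ of NOK 500,000, 750,000 and 1,000,000, to span the unstated current value. The values of ΔC and ΔQALY below are illustrations.

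**Algebra.** CIPE is worth adopting at λ if the net monetary benefit, NMB = λ × ΔQALY − ΔC, is above zero, that is, if λ × ΔQALY > ΔC. Dividing by ΔQALY gives:
- ΔQALY > 0: ICER < λ, which is the written rule.
- ΔQALY < 0: ICER > λ, the reverse of the written rule.

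**Worked cases at λ = NOK 500,000.**

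| Case | ΔC | ΔQALY | ICER | Written rule | NMB | Rule correct? |
|---|---|---|---|---|---|---|
| Costlier, more effective | +5,000 | +0.02 | 250,000 | accept | 10,000 − 5,000 = +5,000 | yes |
| Costlier, more effective | +30,000 | +0.02 | 1,500,000 | reject | 10,000 − 30,000 = −20,000 | yes |
| Cheaper, more effective | −5,000 | +0.02 | −250,000 | accept | 10,000 + 5,000 = +15,000 | yes |
| Costlier, less effective | +5,000 | −0.02 | −250,000 | accept | −10,000 − 5,000 = −15,000 | no |
| Cheaper, less effective, small saving | −5,000 | −0.02 | 250,000 | accept | −10,000 + 5,000 = −5,000 | no |
| Cheaper, less effective, large saving | −30,000 | −0.02 | 1,500,000 | reject | −10,000 + 30,000 = +20,000 | no |

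Every decision in the table is the same at λ = 750,000 and 1,000,000. In 200,000 random combinations (ΔC within ±50,000, ΔQALY within ±0.05, λ from 500,000 to 1,000,000), the rule agreed with NMB in all 100,187 with ΔQALY > 0 and in none of the 99,813 with ΔQALY < 0.

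**Size.** The rule is wrong exactly when ΔQALY < 0. The share misclassified is therefore P(ΔQALY < 0) = Φ(−mean/SE) for a normal distribution, whatever the positive λ. The article gives neither mean nor SE, so these are assumptions:

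| Mean ΔQALY | SE | −mean/SE | Share misclassified |
|---|---|---|---|
| 0.01 | 0.03 | −0.33 | 37% |
| 0.03 | 0.03 | −1.0 | 16% |
| 0.03 | 0.02 | −1.5 | 7% |
| 0.05 | 0.02 | −2.5 | 0.6% |

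**Secondary point, baseline utility.** Randomization is stratified by crisis team only, so mean utility at T1 may differ between arms by chance. T1 falls 4 to 7 weeks after the trauma and T4 at 12 months, so the interval is about 45 to 48 weeks. If an assumed imbalance of 0.03 persisted throughout, it would add 0.03 × 45/52 = 0.026 to 0.03 × 48/52 = 0.028 QALY to an unadjusted difference of arm means.

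**The case against.** The strongest reply is that the sentence is common shorthand for the costlier, more effective quadrant, and that its wording sets a condition needed for acceptance without promising to accept every ratio below the threshold. On that reading a dominated CIPE is not automatically accepted. This is fair, and analysts would probably notice a dominated point estimate. But the text states neither the restriction nor a further condition. Even as a necessary condition, the rule wrongly rejects the case of a large saving with a small QALY loss.

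Three stronger readings are tempting and should not be adopted.

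- A reader might infer that the plan cannot tell dominance from being dominated. The ratio alone cannot, but the article obtains ΔC and ΔQALY separately, and H7 defines dominance by those two parts. The signs will be visible.
- A reader might infer that the reported probability of cost-effectiveness will be badly inflated. With ΔQALY 0.01 (SE 0.03), ΔC NOK 3,000 (SE 8,000) and λ = 800,000, all assumed, the rule accepts 89% of draws while NMB is positive in 58%. That gap comes from assuming an effect one third of its SE. At ΔQALY 0.05 (SE 0.02) the figures are 98.5% and 98.1%. The article does not say that the rule is applied to each draw, or how draws are summarised.
- A reader might infer that the QALY difference is a raw one that ignores baseline. The article does not call the arm means unadjusted, gives no QALY formula, and elsewhere refers to change in QALYs. The assessment schedule is in a figure that is not shown. Covariates may properly be left to an analysis plan, so this is a suggestion for improvement and not an error.

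**Conclusion.** The point holds as a defect in a stated rule. As written, the acceptance criterion is correct for every result with ΔQALY > 0 and wrong for every result with ΔQALY < 0, at any positive threshold. This rests on algebra alone and needs no assumption about the trial.

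Its practical size does depend on assumptions. If the estimated ΔQALY is clearly positive, as the trial expects, the decision on the point estimate is unaffected. Otherwise the exposure equals P(ΔQALY < 0), from under 1% to about 37% over the assumed range above. For the probabilistic analysis this counts only if the rule is used draw by draw. Because H7 is a secondary hypothesis and the remedy is a change of wording, the importance is minor to moderate. It is still worth correcting before the economic analysis starts.

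**What to change.** Replace the acceptance sentence with a net-benefit rule: accept CIPE if λ × ΔQALY − ΔC > 0, with λ the price-adjusted threshold already chosen. Apply the same criterion to each draw of the probabilistic analysis. Report dominance, in either direction, from the signs of ΔC and ΔQALY. Quote an ICER as a decision figure only when both differences are positive.

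As a secondary, low-cost improvement, estimate ΔQALY by regression on arm with adjustment for T1 utility, where that is collected, in place of a plain difference of arm means.

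The cost is a few lines of text and a standard calculation on the same data. The trial status section reports recruitment as ongoing, with completion estimated for September 2026, so the change can be made before analysis.

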### Power and sample size calculations

Previous CIPE studies report effect sizes within the range of *d* = 0.6–0.8. For the primary hypothesis in this study, a more conservative effect size of *d* = 0.3 is expected. With 95% power and an *α*-level of 0.05, 150 participants (73 in each group minimum) are required to detect a significant between-group effect. Consequently, assuming a 20% data attrition rate, at least 183 participants should be recruited. The municipal crisis teams involved in the study currently cover approximately 1,080,000 inhabitants. Although official statistics on the number of traumatic events handled by these teams are lacking, based on the best unofficial statistics available, a conservative estimate suggests 0.5 to 1 case per 1000 inhabitants annually. With a cautious estimate of 0.5, and with each incident involving a mean of two victims aged 16 or older, about 2150 victims are eligible for recruitment over 2 years. Moreover, we assume a ~50% response rate [75] and that approximately 30% have PTSD symptoms 1 month after the incident [76]. These parameters result in a sample of 360 participants, which constitutes the recruitment target. Assuming an overall attrition rate of 40%, 216 participants will complete the 12-month follow-up assessment.

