Key Inclusion and Exclusion Criteria	Inclusion Criteria: Receives support from a municipal crisis team • Exposure to a traumatic event (as defined by criteria A for the diagnosis of post-traumatic stress disorder (PTSD) in the DSM-5) within the last seven weeks before randomization • A total score of 10 or above on the PTSD Symptom Checklist-5 at the time of randomization • Age 16 or above • Written informed consent • Writes and speaks English and/or Norwegian Exclusion Criteria: • Severe psychopathology in need of specialized health care (e.g., psychotic symptoms, or high suicide risk) or substance dependence syndrome in need of specialized health care • Known or evident severe cognitive impairment • Ongoing traumatization, violence, or threats • Unstable dose of psychotropic medication two weeks prior to randomization • Concurrent therapy elsewhere before randomization,
Study Type	A hybrid Type 1 effectiveness and implementation randomized controlled trial.RCT design: parallel two-armed multicenter randomized controlled superiority trial, designed to randomize participants to either CIPE + treatment as usual (TAU) or TAU only.
Date of First Enrollment (planned)	September 15th 2024.
Sample Size	Power analysis: N = 150
Primary outcome(s)	PTSD Checklist for DSM-5 (PCL-5)
Key Secondary outcome(s)	- Clinician-Administered PTSD Scale for DSM-5 (CAPS-5) - Patient Health Questionnaire (PHQ-9) - Insomnia Severity Index (ISI) - Client Satisfaction Questionnaire (CSQ-8) - The EuroQol 5‑Dimension 5‑Level questionnaire (EQ-5D-5L) - The Recovering Quality of Life (ReQoL) - Traumatic grief inventory self report (TGI-SR+)
Ethics Review	The trial is approved by the Regional Committee for Medical and Health Research Ethics (REK-sør-øst, #708906) on 23.05.24, and is conducted following guidelines of good clinical practice (GCP) in accordance with the principle of the Declaration of Helsinki. All participants provide written informed consent before enrollment.
Individual Trial Participant Data sharing statement	In accordance with the ethical approval, deidentified individual clinical trial participant-level data is available from the trial PI upon reasonable request.

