### Trial design

The EASE study is a hybrid Type 1 effectiveness and implementation trial [28] (for implementation, see section “implementation trial”). The first part of the study is a parallel two-armed multicenter randomized controlled add-on superiority trial, designed to randomize participants to either CIPE + TAU or TAU only (ratio 1:1). All participants will be offered ordinary crisis team services throughout the trial period. The CIPE group will be given CIPE as an add-on between T1 (4–7 weeks after trauma, dependent on the time of enrollment) and T2 (10–13 weeks after trauma, dependent on the time of T1 [i.e., T2 is always 6 weeks after T1]; see Fig. 1). For those included within 3 weeks from the incident, a screening assessment is performed at the time of recruitment (T0). Baseline assessment and evaluation of inclusion and exclusion criteria will be completed at T1. Outcome measures are gathered 6 weeks post randomization (T1), and follow-up measurements are accomplished at 6- and 12-month post PTE. This trial follows the SPIRIT guidelines and methodology [29] (see Additional file 1 for the SPIRIT checklist).

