### Randomization

Eligible participants are randomized 1:1 in random block sizes of 4, 6, or 8 to either CIPE + TAU or TAU only, using the Sealed Envelope software [36] at T1. To mitigate the risk of contamination across treatment conditions, participants from the same household are cluster-randomized. The randomization is stratified on the level of municipal crisis teams to ensure an even distribution of cases in each treatment condition across municipalities. An independent, blinded senior researcher is responsible for all randomization procedures. The allocation is revealed to the study coordinator only after the T1 assessment and decision of inclusion are completed.

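### The sample size does not match its stated effect: 73 per arm gives about 44% power for d = 0.3, not 95%; it is the size for d = 0.6

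*Protocol article*

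**What the plan says.** All the inputs stand together in the section on power and sample size calculations of the protocol article.

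- Earlier evidence: "Previous CIPE studies report effect sizes within the range of *d* = 0.6–0.8".
- Planning effect for the primary hypothesis: "a more conservative effect size of *d* = 0.3 is expected".
- Error rates: "With 95% power and an *α*-level of 0.05". Sidedness is not given.
- Result: "150 participants (73 in each group minimum) are required to detect a significant between-group effect".
- With 20% attrition this becomes a minimum of 183 recruited.

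The same section sets a recruitment target of 360, built from catchment population, response rate and symptom prevalence rather than from power. It expects 216 participants to complete the 12-month assessment.

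The structured summary repeats the figure as its sample size: "Power analysis: N = 150". The safety section sets the internal pilot at 18 participants, described as a tenth of the power-based target, which fits 183.

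**The concern.** The plan presents d = 0.3 as a cautious step down from 0.6–0.8. Halving the effect size roughly quadruples the required sample, so a cautious d = 0.3 at 95% power should lead to several hundred participants. A total near 150 is what the earlier, larger effects would need.

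The interpretation of the trial is at stake. A null result from about 150 analysed participants would be read as strong evidence against a small effect, when a true d = 0.3 would be missed more often than detected. The plan also treats 183 as an adequate minimum, so a trial that stopped near that number would look fully powered. The article itself lists delayed recruitment among its limitations.

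**Working it through.** **Inputs.** d = 0.3, power 0.95, alpha 0.05, 73 per arm minimum, 150 in total, 20% attrition, target 360 (power section); 1:1 allocation (randomization section); primary outcome at T2 (data collection section). Two-sided testing is assumed because the article does not say.

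**1. Which base figure the plan used.** 2 × 73 = 146, and 146/0.8 = 182.5, which rounds up to the plan's 183. By contrast 150/0.8 = 187.5, or 188. So 73 per arm is the base, and 150 is that figure rounded up.

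**2. Size required for d = 0.3.** The normal approximation is n per arm = 2(z₀.₉₇₅ + z₀.₉₅)²/d².

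- d = 0.3: 2(1.960 + 1.645)²/0.09 = 288.8, so 289. The noncentral t gives 289.7, so 290 per arm and 580 in total.
- d = 0.6: 2(1.960 + 1.645)²/0.36 = 72.2, so 73. The noncentral t gives 73.2.

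The stated 73 is reproduced with d = 0.6 and not with d = 0.3.

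**3. Power at the stated size.** The noncentrality is d√(n/2). For d = 0.3 and n = 73 it is 0.3 × √36.5 = 1.81, below the critical value of about 1.96, so power is under one half.

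| Analysed per arm | Where it comes from | Power at d = 0.3, two-sided |
|---|---|---|
| 73 | stated minimum | 43.7% |
| 75 | 150 in total | 44.6% |
| 91.5 | 183, no loss | 52% |
| 108 | 216 completers at 12 months | 59% |
| 144 | 360 less 20% | 72% |
| 180 | 360, no loss | 81% |

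At d = 0.6, 73 per arm gives 95.0% and 75 gives 95.5%. With 73 to 75 per arm the detectable effect is about 0.60 at 95% power and 0.46–0.47 at 80%. For d = 0.3, 80% power needs 175.4 per arm and 90% needs 234.5.

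**4. Readings that might rescue 95% at d = 0.3 and 73 per arm.**

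- *One-sided test:* power 56%; 242 per arm would be needed.
- *Baseline adjustment*, effective effect d/√(1 − r²), with r the baseline-to-T2 correlation: 55% at r = 0.5, 61% at 0.6, 71% at 0.7, 85% at 0.8. Reaching 95% needs r of about 0.87. The article gives no correlation, and its model lists group and three post-baseline times with no baseline term.
- *Average of the three post-baseline scores*, effective effect d/√((1 + 2ρ)/3), with ρ the correlation between scores and d = 0.3 at every time: 52% at ρ = 0.7, 60% at ρ = 0.5, and 88% even at ρ = 0.
- *Group-by-time interaction, two measurements, correlation 0.5, f = 0.15:* this returns 146 to 148 in total. In a two-by-two layout with equal baselines, however, f = d/4, so f = 0.15 means d = 0.6. For d = 0.3, f = 0.075; power at 146 is 43.7% and the required total is 580.
- *One-sample or paired t-test at d = 0.3:* 146.3, so 147 in total, but this is not a between-group test.

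**The case against.** The strongest objection is that 44% is not the power of the model in the statistical analyses section. Its first step has a group effect and time but no interaction, so it pools over T2, 6 and 12 months. If d = 0.3 held at all three times, power at 73 per arm would be 52% to 60% for ρ between 0.7 and 0.5. That is fair, and the 44% should be labelled as the unadjusted single-time comparison. T2 is nevertheless the stated primary time point, and the pooled figure is still far from 95%.

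Second, the source of the error cannot be established. The match with d = 0.6 is numerical, and a paired test at d = 0.3 gives a similar total. This stands: the effect, the power or the N could be the misstated item. It does not make the three agree.

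Third, the planned trial is 360, not 150. This softens the consequence: harm from the misstatement is greatest if recruitment falls short. But 360 is a feasibility figure, the plan names 183 as its minimum, and even 360 does not give 95% power for d = 0.3 in the unadjusted comparison.

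Fourth, any figure with baseline adjustment describes an analysis that the article does not state. This also stands, and such figures are conditional on changing the model.

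**Conclusion.** The concern holds. The stated effect, power and sample size contradict one another within one short passage. With d = 0.3 and two-sided alpha 0.05, 73 to 75 per arm gives 44% to 45% power for the T2 comparison, and 95% power needs about 580 analysed, roughly four times the stated number. The stated size is consistent with d = 0.6.

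The headline figure assumes an unadjusted comparison of two means at T2 with independent participants. Households are randomized as clusters, which would lower power further; the article gives no cluster size or intraclass correlation, so the amount cannot be stated. This is not a detail left to a fuller document: the article prints a figure that its own inputs do not support, and uses it in the structured summary and to size the internal pilot.

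**What to change.** Correct the power section and the sample size entry of the structured summary so that effect, power and N agree. Suggested wording: 73 to 75 analysed per arm gives 95% power for d = 0.6 and about 45% for d = 0.3.

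If d = 0.3 remains the planning effect, drop the 95% claim and the statement that 150 are required, and base the power statement on the existing target: 360 randomised with 20% attrition leaves 144 per arm, about 72% power unadjusted. If baseline PCL-5 is added to the primary model, the same 144 per arm gives about 83% at r = 0.5 and 89% at r = 0.6. Those correlations are assumptions and should be labelled as such. The minimum of 183 and the reference to a power-based target in the safety section should be brought into line. Any registry entry that repeats the calculation should be updated too; the registry record was not available for this review.

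The cost is rewording and a less favourable stated power. Quoting the adjusted figures also requires specifying the baseline term. No enrolment beyond the current target is needed, provided the investigators accept the power which that target gives.

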#### Safety and monitoring procedures for adverse events

Despite the lack of severe adverse events (AE) in a recent RCT of CIPE [17], the trial has established procedures to monitor AEs and serious adverse events (sAE). Health personnel in the crisis teams are instructed to monitor and address AE continuously. Unmet healthcare needs that are discovered by the research teams in the T1–4 assessments are communicated to the individual’s therapist in the municipality. Moreover, self- and clinician-reported (s)AE are assessed at T2 (see instruments). Adverse events are defined as any unfavorable experience occurring to participants during the trial. Serious adverse events are defined as incidents including death, (attempted) suicide, serious self-harm, acute mania or psychosis, severe intoxication, or other psychological or somatic conditions requiring emergency medical care.

After the first 18 participants are randomized (corresponding to 10% of the target sample size based on the power analysis), an internal pilot study will be conducted in accordance with the CONSORT guidelines for randomized feasibility and pilot trials [77, 78]. The pilot will assess AEs and sAEs. If the rate of AEs is substantially higher than reported in previous studies of CIPE and/or any sAEs occur, the advisory board will consider protocol modifications and/or discontinuation of the trial. Should such deliberations arise, the project owner will retain the final authority to decide whether the trial will be terminated.

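### The recruitment target of 360 does not follow from the stated inputs, which give 324; the minimum of 183 also falls slightly short of the 150 called required

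*Protocol article*

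**What the plan says.** The section Power and sample size calculations in the protocol article contains two separate chains of numbers.

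The first is a power requirement. The article states that 150 participants, with a minimum of 73 per group, are needed, and then that "assuming a 20% data attrition rate, at least 183 participants should be recruited".

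The second is a recruitment forecast. It starts from the catchment ("The municipal crisis teams involved in the study currently cover approximately 1,080,000 inhabitants") and an incident rate ("a conservative estimate suggests 0.5 to 1 case per 1000 inhabitants annually"), of which the lower value is used. It continues: "with each incident involving a mean of two victims aged 16 or older, about 2150 victims are eligible for recruitment over 2 years". A response of roughly 50% and a prevalence of PTSD symptoms of roughly 30% are then applied. The result is given as: "These parameters result in a sample of 360 participants, which constitutes the recruitment target". With 40% overall attrition, the article expects that "216 participants will complete the 12-month follow-up assessment".

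Two other places carry a sample size. The Sample Size row of the structured summary reads "Power analysis: N = 150". The section Safety and monitoring procedures for adverse events sets an internal pilot after 18 randomized participants, described as "corresponding to 10% of the target sample size based on the power analysis".

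**The concern.** The article presents 360 as the product of the parameters listed just before it, and a reader who multiplies them does not get 360. The expected number at 12 months is taken directly from 360, and hypotheses H1, H2, H3 and H5 are all assessed at 12 months, so an optimistic forecast carries into the follow-up numbers.

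The minimum of 183 is introduced as a consequence of needing 150, yet at the stated attrition it does not deliver 150.

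The word target is attached to 360 in one section and to a power-based figure of about 183 in another, while the structured summary lists only 150. Someone reading a single section could therefore take away a different planned size from someone reading another. Recruitment was still open when the article was written, with completion estimated for September 2026, so these figures can still be corrected while they are in use.

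**Working it through.** **Inputs**, all from Power and sample size calculations: 1,080,000 inhabitants; 0.5 incidents per 1000 inhabitants per year (stated range 0.5 to 1); 2 victims per incident; 2 years; about 50% response; about 30% with symptoms; 40% attrition to 12 months; 150 required in total and 73 per group minimum; 20% attrition for the power-based minimum.

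**Step 1, pool of victims.**
1,080,000 × 0.5/1000 × 2 × 2 = 2,160. The article says about 2150, so this step reproduces.

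**Step 2, expected sample.**
Pool × response × prevalence:
- from 2,160: 2,160 × 0.50 × 0.30 = 324
- from 2150: 2,150 × 0.50 × 0.30 = 322.5

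The stated 360 does not reproduce. The excess is 36 participants: 36/324 = 11.1% (37.5/322.5 = 11.6% from the rounded pool). Since step 1 reproduces, the discrepancy lies in this last multiplication or in the values used for it.

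**Step 3, what would give 360.**
- Prevalence at 50% response: 360/(2,160 × 0.50) = 33.3% (33.5% from 2150)
- Response at 30% prevalence: 360/(2,160 × 0.30) = 55.6%
- Upper incident rate of 1 per 1000: 1,080,000 × 1/1000 × 2 × 2 × 0.50 × 0.30 = 648, so this does not explain 360 either

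**Step 4, completers at 12 months.**
- 360 × (1 − 0.40) = 216, which reproduces the article's figure exactly
- 324 × (1 − 0.40) = 194.4, about 194

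The attrition step is correct. Only its starting value is in question.

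**Step 5, power-based minimum.** N/(1 − attrition):
- 2 × 73 = 146; 146/0.80 = 182.5, rounded up to 183, the article's figure
- 150/0.80 = 187.5, rounded up to 188
- in reverse, 183 × 0.80 = 146.4

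The 183 was built on the per-group minimum, not on the 150 in the same passage. The gap is 188 − 183 = 5 participants.

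**Step 6, which number the pilot refers to.**
10% of 183 = 18.3; 10% of 150 = 15; 10% of 360 = 36. The 18 fits 183, so target in the safety section means the power-based minimum, not the 360.

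**Step 7, does the correction breach the plan's own minimum?**
324 > 188 and 194 > 150. It does not.

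**The case against.** The strongest reply is that the inputs are marked as approximate. With a prevalence of one third instead of 30%, 2,160 × 0.50 × 1/3 = 360 exactly, so a rounded input is as plausible as a wrong product. The article also admits that official statistics are lacking, and its own range for the incident rate moves the forecast from 324 to 648, which dwarfs an 11% gap. This stands as far as it goes: the documents do not show whether the input or the output is at fault. It does not rescue the sentence, because the parameters as printed do not give 360.

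The mismatch between 183 and 150 is small, and 183 follows exactly from the minimum of 73 per group. That also stands, and it is why this part is secondary.

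Three stronger readings are tempting, and the documents do not support them:
- **That 216 is a further arithmetic error.** It is exactly 60% of 360 and only inherits the first discrepancy.
- **That recruitment could be stopped at whichever of 150, 183 or 360 suits.** The three carry different labels: required by the power analysis, minimum to recruit, and recruitment target. The safety section qualifies its own use of target as power-based. The only interim review described is the pilot, which assesses adverse events, and no efficacy look is described. What remains is inconsistent wording.
- **That the trial's power is overstated because 360 is too high.** The article's only power statement concerns 150 participants, and it claims no power for 360. Whether 150 itself follows from the assumed effect size is a separate question that this point does not address.

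**Conclusion.** The point holds as a correction of stated figures. On the printed inputs the expected sample is 324 (322 from 2150), so 360 is about 11% too high, and the expected 12-month completers are about 194, not 216. The minimum of 183 yields 146 analysable participants against 150 called required; 150 would need 188.

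This rests on taking the response and prevalence at their printed values of 50% and 30%. If the authors used about 33% or about 56% respectively, 360 is right and the printed input is wrong; either way the passage needs correcting. The consequence is limited, since the corrected forecast stays above the plan's own minimum even at 12 months, taking the 150 as the article states it.

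**What to change.** 1. In Power and sample size calculations, either restate the expected sample as 324 and the 12-month completers as 194, or keep 360 and 216 and state and justify the response or prevalence that produces them.
2. In the same section, change 183 to 188, or change 150 to 146. If 146 is chosen, change the Sample Size row of the structured summary to match.
3. Use the word target for one number only. Call the power-based figure in the structured summary and in the safety section the minimum.
4. Leave the pilot safety review at 18 participants and change only its description. The article ties the 18 to the power-based figure. Re-basing the 10% on 324 or 360 would move the review to about 32 or 36 participants, a change in safety monitoring that this correction does not call for.

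The cost is wording in the protocol, and in the registry entry if it carries the same figures. The forecast becomes slightly less favourable. No design feature or analysis changes.
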